## 7.5 Study methodology

All testing and analysis involved in this study will be completed at The Children's Hospital at Westmead or the BASE Facility of Monash University. Procedures will be the same across sites, unless otherwise indicated. Participants will complete the following testing as part of the trial:

- 1. Anthropometry:** Weight, height and waist circumference will be measured by an appropriately trained assessor blinded to treatment allocation, using standard protocols [38]. At 24-months participants will be asked to self-report their height and weight in an online questionnaire prior to their follow-up appointment; those who attend an on-site appointment will also have height and weight measured by a trained assessor.
- 2. Bioelectrical impedance analysis:** Will be used to measure body composition. A stand-on Seca 515 scale will be used at Monash University and the Monash Children's Hospital and a Tanita MC780MA body composition analyser will be used at The Children's Hospital at Westmead.
- 3. Dual energy x-ray absorptiometry (DXA):** This non-invasive procedure, with a very low-dose radiation exposure, will be used to measure body composition and fat mass. At The Children's Hospital at Westmead the Prodigy, Lunar-GE DXA (Madison, WI USA) will be used.

At Monash, the GE iDXA (Madison, WI, USA) will be used. Core scan software on the GE iDXA will be used to measure visceral fat in the Monash cohort.

- 4. Psychological outcome questionnaires:** A range of psychological outcomes will be assessed using validated tools that are commonly used in this age group. [name] will lead this component of the study. The questionnaires take approximately 30-40 minutes to complete on an iPad with REDCap survey software. The psychometric questionnaires that will be used are:

- Eating Disorder Examination Questionnaire (EDE-Q) [39]
- Body Appreciation Scale [40]
- Weight Bias Internalisation scale [41]
- Binge Eating Scale [42]
- Rosenberg Self-Esteem Scale [43]
- Centre for Epidemiologic Studies Depression Scale Revised (CESDR-10) [44]
- Quality of Life using Impact of Weight on Quality of Life – Kids [45]
- Dutch Eating Behaviour Questionnaire (DEBQ) [46]
- Depression Anxiety Stress Scale (DASS-21) [47]

The EDE-Q will be used as a screening tool at baseline to identify participants with an undiagnosed eating disorder requiring treatment prior to participation in a weight management study. Participant will be assessed and referred as per standard clinical practice.

The CESDR-10 will be used as a screening tool at baseline to identify participants at high risk of clinical depression requiring referral for further assessment.

- 5. Dietary assessment:** Diet quality, food choices and food patterns will be assessed using the Australian Child and Adolescent Eating Survey (ACAES)[48, 49], a validated self-administered, semi-quantitative food frequency questionnaire, which takes ~15 minutes to complete and provides immediate analysis of the results and comparison of food and nutrient intake with nutrition targets. Participants will complete the survey at baseline, week 16, week 52 and at 24-month follow-up. They will be sent a personalized link to the tool. Participants may complete the survey at home or on an iPad at their dietitian visits.
- 6. Sedentary behaviour, physical activity and sleep quality:** will be assessed using validated tools appropriate for this age group. The questionnaires will be completed on an iPad using RedCap software. The questionnaires that will be used are:
- Godin Leisure-time Questionnaire [50]
  - Pittsburgh Sleep Quality Index [51]
- 7. Blood pressure:** Systolic and diastolic blood pressure will be measured using an automated monitor under standardised conditions by trained study personnel blinded to treatment allocation.
- 8. Biochemistry:** A 20 mL fasting blood sample will be collected to measure high-sensitivity CRP, lipids (total triglycerides and high-density and low-density cholesterol), glucose and insulin levels, and liver function. As poor renal function is a contraindication for initiating a VLED plan,

urea and electrolytes (UEC) will be measured at baseline. All blood samples will be collected by trained personnel using standard operating procedures. The Children's Hospital at Westmead will also store a 10mL sample of blood for later analyses of a range of known (e.g. gut hormones and peptides (leptin and ghrelin) and metabolomics) and unknown (novel) biomarkers related to obesity and cardio-metabolic risk. These blood samples will be stored at Westmead Biobank. BASE at Monash University will store 2mL of the 20mL fasting blood samples as serum for later analyses of hormones and metabolites related to obesity.

- 9. Inflammatory markers and RNA extraction:** 4 mL (from the 20mL) fasting blood sample will be stored within the Monash cohort to measure a range of inflammatory markers (adiponectin, HGF, IL-1 $\beta$ , IL-6, IL-8, leptin, MCP-1, NGF, PAI-1 (Total), resistin, TNF- $\alpha$ ) and for RNA extraction. Blood samples will be collected by trained personnel using standard operating procedures.
- 10. Adherence:** Ketones will be measured to assess adherence to the VLED protocol and IER plan. Blood ketones will be measured weekly during Phase 1, using the Freestyle Optium Neo Blood Glucose and Ketone Monitoring System. Ketones will also be measured using the Freestyle Optium Neo for the IER group only at week 16 and 52.
- 11. Diet review:** Participants will be asked to complete the Automated Self-Administered 24 hour dietary assessment tool (ASA24-Australia) at baseline, week 12 and week 36. This will assess diet quality and adherence. Participants will be sent an individualized link to log into the assessment tool online. They may complete this in their own time at home or before their appointment with the dietitian. It will take approximately 30 minutes to complete. Additionally, weekly diet reviews will be conducted by the study dietitian until the end of phase 1, then reviews will reduce gradually throughout phases 2 and 3 (see Figure 2). Diet reviews will be used to assess adherence (24 hour recalls, as used in the RESIST study – HREC:07/CHW/12) [37], identify and address any problems following the diets, ensure adequacy of the diet and set goals for participant. As part of nutrition therapy, acceptability is monitored and support provided. The protocol is flexible and food preferences will be considered by the dietitian within the 'My Meal Plan' and Phase 3 Step-down diet intervention.
- 12. Acceptability:** Participant views relating to acceptability of the diet intervention, program satisfaction and feedback will be collected in questionnaires at 4, 16 and 52 weeks. The questionnaires that will be used are:
  - Participant acceptability questionnaire
- 13. Clinical assessment and review:** Prior to enrolment, all participants will have a clinical assessment to determine eligibility. This may be completed by a referring clinician or study doctor. A follow up medical review of participants by Junior or Senior Medical Officers at both hospitals will occur at 16 weeks unless otherwise indicated. Where participants are identified as requiring additional medical review outside of major outcome visits, these appointments should occur face-to-face.
- 14. Psychological Assessment:** Some participants may require a review by the study psychologist. This will occur if the participant has been flagged as 'at risk' by study clinicians or screening/monitoring procedures and should occur face-to-face.

**15. Resting Energy Expenditure (Monash Only):** Resting energy expenditure (REE) will be measured by indirect calorimetry and will be used to assess the compensatory mechanisms associated with weight loss and REE. It will take approximately one hour to complete the measures. It will not be essential for participants to complete this assessment and will have the opportunity to decline participating in this procedure. Subjective feelings of hunger and satiety using Visual Analog Scales will be collected via an iPad prior to REE being measured. This takes two to three minutes for participants to complete.

**16. Intervention Fidelity:** Intervention fidelity will be evaluated using the framework developed by Carroll et al. [26]. Table 3 provides a summary of Methodology used for measuring Intervention Fidelity. Data will be collated and analysed quantitatively using SPSS software.

**17. Gene Expression (Monash Only):** Gene expression will be measured by RNA sequencing and will be used to assess relationships between gene expression changes and weight loss. This investigation is of an exploratory nature. This analysis is optional for participants.

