## 7.9 Screening Assessment

Screening assessments will be completed for all participants prior to enrolment. This may be completed as a standalone appointment or combined with the baseline visit.

The following must be done to confirm eligibility:

1. **Clinical assessment:** All participants will be assessed by a referring clinician or the study doctor.
2. **Biochemistry:** Fasting insulin, glucose, LFTs and lipids will be reviewed by the study doctor. At the on-site screening appointment all parents and adolescents will also be asked whether they consent to the adolescent's screening pathology results being used in analyses (irrespective of whether they are eligible to enrol).
3. **Blood Glucose Levels:** Trained personnel may also measure blood glucose levels via a finger prick blood sample using the Freestyle Optium Neo Blood Glucose and Ketone meter. This is to identify participants who may have undiagnosed Type 2 Diabetes. Participants will be excluded from the study if:
  - a. Fasted blood glucose >7mmol/L
  - b. Random blood glucose >11.1mmol/L
4. **Screening questionnaires:** The EDE-Q and CESDR-10 will be used to screen participants for eating disorders and depression. The questionnaires will be completed prior to enrolment in the study and are repeated at weeks 4, 16 and 52. Screening questionnaires are emailed to potential participants prior to attending an on-site appointment. At the on-site screening appointment all parents and adolescents will also be asked whether they consent to the adolescent's screening questionnaire data being used in analyses (irrespective of whether they are eligible to enrol). Should a participant complete screening questionnaires without attending an on-site appointment to provide consent, data collected will not be included in analyses.
5. **Psychological assessment:** A psychologist may be involved in participant assessment prior to enrolment. This will be based on screening questionnaires and input from the study doctors or dietitians.

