**Please note:** If a recent blood test (taken in the previous 8 weeks) is available, this will be used to confirm eligibility. Alternatively, a fasting blood sample may be collected by trained personnel prior to a participant's enrolment in the study. This will include collection of bloods for storage. A consent form must be signed prior to the collection of fasting bloods. Stored blood samples collected for individuals who do not progress to enrolment will be destroyed immediately.

If the inclusion and exclusion criteria are met to the satisfaction of the reviewing practitioner/s, the participant will be enrolled into the study. Ineligible participants will be asked if they would like to be contacted by investigators in the future if suitable studies arise that may be of benefit to them.

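### UEC, the test for the protocol's own VLED contraindication, is not among the eligibility bloods, so the VLED may start before its result is known

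*Protocol*

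**What the plan says.** Section 7.5, item 8 (Biochemistry) states "As poor renal function is a contraindication for initiating a VLED plan" and, as the consequence, that "urea and electrolytes (UEC) will be measured at baseline".

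Section 7.9 is the operative eligibility section. Under the lead-in "The following must be done to confirm eligibility", item 2 reads "Fasting insulin, glucose, LFTs and lipids will be reviewed by the study doctor". On timing, the section says of the screening assessment: "This may be completed as a standalone appointment or combined with the baseline visit". On the source of the bloods it says "If a recent blood test (taken in the previous 8 weeks) is available, this will be used to confirm eligibility", followed by "Alternatively, a fasting blood sample may be collected by trained personnel prior to" enrolment. A participant who meets the inclusion and exclusion criteria to the reviewing practitioner's satisfaction is then enrolled.

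Section 7.8 lists ten exclusions. The nearest to renal function is the general one for significant medical or psychiatric illness.

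Section 7.4 places randomisation after the screening visits, and section 7.2.1 places it at baseline. Section 7.2.2 has Phase 1, the VLED of about 800 kcal/day, run from baseline for up to 4 weeks in all participants of both arms.

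**The concern.** The protocol ties the contraindication to initiating the diet. The UEC test therefore serves its stated purpose only if someone reads the result before the first VLED day. Nothing in the eligibility rule makes that happen: UEC is ordered in the methodology section, while the section that decides who is enrolled lists other bloods and leaves it out.

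At stake is the safety of participants aged 13 to 17. A site following section 7.9 to the letter could put a participant with unrecognised renal impairment on a severe diet before the protocol's own contraindication has been checked. Because the VLED is common to both arms, this does not depend on the allocated diet.

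**Working it through.** No figure in the plan is in dispute and no power or sample-size arithmetic applies. The check is a comparison of sections.

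**Counts**

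- Bloods to be reviewed for eligibility (7.9, item 2): insulin, glucose, LFTs, lipids. UEC is 0 of 4.
- Exclusions (7.8): secondary obesity; intellectual disability; medical or psychiatric illness; previous type 2 diabetes; eating disorder under treatment; pregnancy; medications affecting weight; poor spoken English; current weight loss program; BMI above 45 kg/m². Renal function is named in 0 of 10.

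**Can a participant reach the VLED with no UEC result?**

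1. A blood test from the previous 8 weeks is available. Section 7.9 says it is used to confirm eligibility and sets no condition that it include UEC. The pre-enrolment fasting sample is only the alternative to such a test.
2. With the remaining screening items done and the criteria met, the participant is enrolled (7.9).
3. Screening may share a visit with baseline (7.9), and randomisation occurs at baseline after screening (7.2.1, 7.4).
4. Phase 1 starts at baseline (7.2.2).
5. UEC is due at baseline (7.5, item 8). On this path its first draw can fall on the day the VLED starts.
6. No section withholds the VLED until the UEC result is read, sets a latest time for reading it, or gives a cut-off or action.

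The path is therefore open. It is not open at every combined visit: without an outside test, the section 7.9 bloods have to be drawn and reviewed before enrolment, so same-day enrolment does not arise in this way.

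**Does the phrase used for timing close the gap?** Section 7.5 also describes the EDE-Q and CESDR-10 as baseline screening tools, so baseline can mean before enrolment. For those two, however, section 7.9, item 4 adds "The questionnaires will be completed prior to enrolment in the study". For undiagnosed diabetes, section 7.9, item 3 goes further and gives exclusion limits (fasted glucose above 7 mmol/L, random glucose above 11.1 mmol/L). UEC has neither a timing line nor a limit.

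**Other places where UEC might be fixed.** It is not in the blood panel of Table 2, nor in the list of analytes in section 10.1. Footnote k to Table 2 says standard bloods at Monash are frozen, batched and processed later. That panel does not name UEC and section 10.1 speaks of immediate analysis, so late processing of UEC at Monash is not established and the conclusion does not rest on it.

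**The case against.** The best answer is that section 7.5 should be read for its purpose. It orders UEC because of the contraindication to initiating the VLED, and a result read after the diet has started would defeat that purpose. On this reading section 7.9 merely lacks a cross-reference, and no sentence tells a site to start before the result is in. The path is also narrow: it needs an outside test within 8 weeks, that test without UEC, a first UEC draw on the day the diet starts, and a clinician who does not wait. Medical safeguards remain. Every participant has a clinical assessment before enrolment, significant medical illness excludes, and the reviewing practitioner has to be satisfied.

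Much of this stands. A check before the VLED was probably intended, the subset may be small, and the safeguards can stop a participant whose renal disease is already known. None of them requires anyone to see a UEC result, and the protocol orders UEC in addition to them, evidently because clinical assessment alone was not thought enough. The intention appears in the methodology section but not in the list of what has to be done before enrolment. That list does contain explicit requirements for glucose and the questionnaires.

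It is also fair to say that a renal exclusion left to the study doctor's judgement largely overlaps with the existing illness exclusion. That part of the fix is the least important.

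**Conclusion.** The concern holds. The stated eligibility rule omits the test for the protocol's own contraindication, so the protocol permits, though it does not require, VLED start before the UEC result is known. The textual size is UEC in 0 of 4 eligibility bloods and renal function in 0 of 10 exclusions. These counts show the omission; they do not measure risk. The participants concerned are those cleared on bloods without UEC, most clearly on an outside test up to 8 weeks old. The documents give neither the size of this group nor the frequency of abnormal UEC, so no number is estimated and no prevalence is assumed.

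The conclusion rests on reading section 7.9 as the complete list of what is required before enrolment, which is how its lead-in presents it. The point should be fixed on participant-safety grounds. It does not bear on the analysis of BMI z-score as far as the documents show.

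**What to change.** - Add UEC to the bloods in section 7.9, item 2.
- Accept an outside test as confirming eligibility only if it includes UEC. Otherwise draw UEC in the pre-enrolment fasting sample that section 7.9 already allows.
- Require the study doctor at both sites to review the UEC result before randomisation and before the VLED starts.
- Name poor renal function, as judged by the study doctor, as an exclusion in section 7.8. This overlaps with the existing illness exclusion but makes the contraindication visible where eligibility is decided.

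The cost is a wording amendment to sections 7.8 and 7.9. The assay is already planned; only its timing and review change. In practice, a participant whose outside test lacks UEC needs a draw before enrolment, some families can no longer complete screening and baseline in one visit, and both sites have to run UEC promptly.

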### Assessments completed by parents

- 1. Demographic:** Parents will be asked to complete a demographic questionnaire at baseline. The results of this will be used to describe the group profile of the Fast Track cohort. They will be asked to answer questions related to ethnicity, socioeconomic status and family medical history. Questions have been adapted from existing questionnaires [52-55]. It will not be essential for parents to answer all questions.
- 2. Acceptability:** Parent views relating to the acceptability of the diet intervention, program satisfaction and feedback will be collected through questionnaires at 4, 16 and 52 weeks. The tool used to assess this will be:
  - Dietary intervention questionnaire (parents)

**Table 3. Summary of methodology for measuring intervention fidelity**

| Implementation Fidelity Measure |                                              | Measure                                                                                                                                                                                                                                                       |
|---------------------------------|----------------------------------------------|---------------------------------------------------------------------------------------------------------------------------------------------------------------------------------------------------------------------------------------------------------------|
| Measures of adherence    | Procedural fidelity                          | Audit of the Dietitian Framework Session Outline checklist                                                                                                                                                                                                    |
|                                 | Exposure or dose
(frequency/
duration) | 
 
• Attendance rates at face-to-face sessions
 
• Total exposure to additional supports via SMS/ telephone/ video teleconference
 
• Facebook data regarding use of the Facebook groups
 
         |
| Moderators of adherence  | Intervention Complexity                      | 
 
• This intervention aims to address a multifactorial problem, comprises of multiple components and is being implemented across multiple sites. It would therefore be regarded as a complex intervention[28]
 
 |
|                                 | Facilitation Strategies                      | 
 
• Audit of training log
 
• Dietitian Feedback Questionnaire
 
                                                                                                                                         |

|  |                            |                                                                                                                                                                                                                                                                                                                                                                                                                                                                   |
|--|----------------------------|-------------------------------------------------------------------------------------------------------------------------------------------------------------------------------------------------------------------------------------------------------------------------------------------------------------------------------------------------------------------------------------------------------------------------------------------------------------------|
|  | Quality of delivery        | 
 
• Completion of Consultation and Relational Empathy (CARE) Measure by Participants at week 36
 
                                                                                                                                                                                                                                                                                                                   |
|  | Participant responsiveness | 
 
• Acceptability questionnaires
 
• 30-60 minute semi-structured interviews with participants, parents/guardians as to practicality and acceptability of the intervention at completion (week 52).
 
• 30-60 minute semi-structured interviews with dietitians to evaluate the practicality and acceptability of intervention. Interviews will be scheduled based on the dietitian's availability.
 
 |

